### Procedure for Unblinding If Needed

Participants will be asked to guess which group they belonged to in the last TPS session to evaluate the success of blinding.

### Data Collection and Management

#### Plans for Assessment and Collection of Outcomes

Both groups will be measured at baseline (T_1_), immediately after the intervention (T_2_), and at the 3-month follow-up (T_3_; refer to Figure 5 CONSORT flow diagram). Based on the previous studies, a 3-month follow-up is sufficient to assess the long-term sustainability of the TPS intervention (60). A trained clinician investigator who is not involved in the intervention will perform the assessments. The primary and secondary outcomes will be assessed at baseline, immediately after the intervention, and 12 weeks after the intervention.

#### Plans to Promote Participant Retention and Complete Follow-Up

A WhatsApp message reminder (e.g., TPS intervention schedule, fMRI scan appointments, and f/u appointments) will be delivered to participants to monitor their progress and adherence throughout the TPS study.

### Data Management

#### Data Management Plan (DMP)

The DMP is enforced according to the Personal Data (Privacy) Ordinance, Code of Ethics for Research Involving Human Subjects, and the Policy on Ownership of Intellectual Property issued by the PolyU. All the anonymized data including fMRI scans, laboratory results and documentation will be converted into.csv, and.pdf formats for long-term preservation and access and stored in a Figshare and PolyU home drive for 5 years with a DataCite DOI as an identifier.

### Confidentiality

All consenting participants will be listed in alphabetical order according to their surnames, and each participant will be assigned a unique study number. All personal information collected for potential and enrolled participants will only be shared under the supervision of the principal investigator. All confidential data will be kept and maintained by the principal investigator after the trial ends in case any emergencies will be raised from participants. The confidential data will be destroyed once publications have been made.

### Plans for Collection, Laboratory Evaluation, and Storage of Biological Specimens for Genetic or Molecular Analysis in This Trial/Future Use

Not applicable.

### Statistical Methods

#### Statistical Methods for Primary and Secondary Outcomes

##### Data Analysis Plan

Data will be analysed by the SPSS for Windows, version 27. The normality of the primary outcome (depression) scores will be tested by the Kolmogorov-Smirnov test. If significant differences between sociodemographic variables are found, covariates will be used as a control or confounding variables in the main analysis. For Objective 1, multilevel modelling analysis will be used to investigate changes in the outcome measures (depression) at each time interval (2 weeks and 3 months) with respect to their baseline measurements to examine the effects of TPS. A two-level model will be built, with repeated time points at level 1 and respondents at level 2. The baseline difference between groups will be tested using the Wald test based on the regression coefficient estimates of the indicator. The changes in the outcome measures over time will be included in the fixed part of the model to estimate change from baseline to 2 weeks and from baseline to 3 months. To assess the effects of TPS over time, interaction terms will be included in the fixed part of the model. The significantly different demographics between groups identified in step one of the analysis and other possible confounders will be adjusted by including them in the main-effect model. The within-respondent random effects of the outcome measurements will be taken into account by the level-2 variance in the model. For Objectives 2, 3, and 4, pairwise comparison and other hypotheses on the intervention effects will be tested using a generalised Wald test with an adequate degree of freedom from the modelling analysis (70). The same model, which will be conducted separately for each outcome, will be used to investigate the effect of interventions on secondary outcome measures. To assess the effects of TPS, an intention-to-treat (ITT) analysis will be performed on all participants who undergo random allocation. A multiple imputation method will be used to handle missing data. The pooled results of the multilevel analyses with five multiple imputations will be presented. A sensitivity analysis will be performed by comparing results from analysis datasets with and without missing data imputation. In all tests, significant differences between groups will be detected with a 95% CI, and *p*-values of < 0.05 (two-tailed) will be considered significant. For Objective 5, the neurological rs-fMRI data, longitudinal VBM will be used to examine whether TPS produces local changes in grey matter. Specifically, relative local increases and decreases between pre- and post-intervention scans will be compared within and between study groups. The diffusion MR data will be analysed using the diffusion tensor model. After a mathematical diagonalization process, the eigenvectors and eigenvalues describing the tensor ellipsoid will be determined. Then, two standard diffusion indices will be obtained which are the following: (1) the apparent diffusion coefficient and (2) the fractional anisotropy. DTI scans pre- and post-treatment will permit the assessment of changes in axial diffusivity, with lower values being interpreted as the structural enhancement of white matter. For the cognitive data analysis, general linear modelling (GLM) will be used to compare the difference in performance in the forward and backward digit span, the Stroop test, the category verbal fluency test, and the TMT Parts A and B between the TPS group and the waitlist control group. Performance on the TMT between the TPS group and the waitlist control group will be analysed by one-way repeated-measures ANOVA. Participants' narrative feedback on TPS will be analysed with descriptive content analysis.

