### Trial Design

In this proposed study, we will use a single-blind randomised controlled trial design with two-armed repeated measures. The trial design complies with the Consolidated Standards of Reporting Trials (CONSORT) statement (61). In our two-armed design, we will use TPS as an intervention group and a waitlist control group. At the same timepoints, we will appropriately compare the effect of the TPS treatment between those who received it in the intervention group and those who did not receive it in the waitlist control group (62). Both groups were measured at baseline (T_1_), immediately after the intervention (T_2_), and at the 3-month follow-up (T_3_). A total of 30 community-dwelling subjects, aged 18 and above, will be recruited. All subjects will be computer randomised into either the intervention group or the waitlist control group, balanced by gender and age on a 1:1 ratio. All subjects in each group will have to undertake fMRI before and after six 30-min TPS sessions, which will be completed in 2 weeks' time. Baseline measurements and post-TPS evaluation of the psychological outcomes (i.e., depression, cognition, anhedonia, and IADL) will also be conducted on all participants. Based on the previous studies, a 3-month follow-up is sufficient to assess the long-term sustainability of the TPS intervention (60).

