## Assignment of Interventions: Allocation

### Sequence Generation

#### Randomisation, Allocation, and Masking

All consenting participants will be listed in alphabetical order according to their surnames, and each participant will be assigned a unique study number. After baseline measurement, randomisation will be conducted by an independent statistician off-site using a stochastic minimisation programme to balance the gender, age, and depression scores of the participants. Eligible participants will be randomised into two groups using a pre-/post-test waitlist control group design. The allocation to the two groups will be 1:1.

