### Concealment Mechanism

An independent statistician will use a computer-generated list of random numbers (www.random.org) to ensure concealment of randomisation. To avoid information flow, participants in both groups will be advised not to reveal their study participants to the other group, to minimise potential contamination of the effects of TPS or subject bias. The participant list will be concealed from the recruitment venues throughout the study.

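### Covariates for the primary model are picked by baseline significance tests, while the minimisation factors and baseline HAM-D-17 are not fixed as adjustment terms; the likely cost is some precision, not false positives

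*Protocol article*

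**What the plan says.** The Data Analysis Plan gives the covariate rule twice. First: "If significant differences between sociodemographic variables are found, covariates will be used as a control or confounding variables in the main analysis". Then, for the main model: "The significantly different demographics between groups identified in step one of the analysis and other possible confounders will be adjusted", by entering them as main effects. It also says: "The baseline difference between groups will be tested using the Wald test based on the regression coefficient estimates of the indicator".

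The primary model is described thus: "A two-level model will be built, with repeated time points at level 1 and respondents at level 2". HAM-D-17 at T1 is one of the repeated outcomes. The effect of TPS is read from interaction terms, that is, from the difference between arms in change from baseline to 2 weeks and to 3 months.

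On allocation, the section Randomisation, Allocation, and Masking has the independent statistician randomise "using a stochastic minimisation programme to balance the gender, age, and depression scores of the participants". Other places differ. The Abstract and Trial Design name two factors only ("balanced by gender and age on a 1:1 ratio"), and Concealment Mechanism says "An independent statistician will use a computer-generated list of random numbers (www.random.org) to ensure concealment of randomisation".

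Nowhere does the article commit to gender, age or baseline HAM-D-17 as a covariate in the primary analysis.

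**The concern.** In a randomised trial a significant baseline difference is a chance event, and its p-value says nothing about whether the variable predicts outcome. A rule that admits covariates on that basis tends to bring in noise and leave out useful predictors. Here it also works against the allocation scheme: a factor used in minimisation is balanced by design, so it is among the least likely to reach p < 0.05 and be adjusted for. An analysis that ignores the balancing factors overstates its standard error. The unnamed further confounders leave a choice open after the data are seen.

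The second part concerns baseline. Because T1 is an outcome and the group difference there is left free (and tested), the contrast is a difference in change scores. It does not use the knowledge that randomisation makes the arms equal in expectation at T1. With 15 per arm, precision given away is hard to recover.

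**Working it through.** **Inputs from the article.** N = 30, 1:1, two-sided 0.05 (Sample Size Estimation; Randomisation, Allocation, and Masking; Data Analysis Plan); nine demographic variables (Demographic Data); HAM-D-17 at T1, T2 and T3. Sample Size Estimation gives no SD, correlation or effect size, so N = 30 has no derivation to reproduce. For scale, 15 per arm gives 80% power for a standardised difference of about 1.06 (t test).

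**Assumptions, not in the article.** Correlation r between baseline and follow-up of 0.3 to 0.7; T1/T2 SDs equal, 5/6 or 4/6; true effect 0.8 SD (or 5 points where stated); in the equal-SD simulation below, gender and age effects of 0.3 SD each and minimisation that follows the balancing choice with probability 0.8.

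**1. What the rule selects.** With independent null variables, the chance of at least one p < 0.05 is 1 − 0.95^9 = 0.37 for nine candidates, and 1 − 0.95^7 = 0.30 for the seven that minimisation does not balance. In 4,000 simulated trials per scenario some covariate was selected in about 30%, but gender or age in under 1%.

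**2. Does selection move the primary result?** With complete data and a random intercept, a covariate that is constant over time affects only the between-person part of the model, and the group-by-time interaction is a within-person contrast. Numerical check: interaction −0.1409 (SE 0.4556) both with and without age and gender as main effects. So it does not. Selection could matter with missing data, with covariate-by-time terms, or in a regression of follow-up scores alone. In that last form, at 0.8 SD, selecting covariates took power from 57.2% to 54.0%, 55.8% to 53.0% and 57.7% to 54.1% at r = 0.3, 0.5 and 0.7.

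**3. Change score against baseline adjustment.** Variance ratio = (s1² + s2² − 2·r·s1·s2) / (s2²·(1 − r²)).
- Equal SDs: this reduces to 2/(1 + r), i.e. 1.54, 1.33 and 1.18 at r = 0.3, 0.5 and 0.7.
- SD 5/6, r = 0.5: (25 + 36 − 30)/(36 × 0.75) = 31/27 = 1.15.
- SD 4/6: r = 0.3, 37.6/32.76 = 1.15; r = 0.5, 28/27 = 1.04; r = 0.7, 18.4/18.36 = 1.00.

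**4. Calibration and power under minimisation, equal SDs, effect 0.8 SD.** The stated random-intercept model is compared with ANCOVA at T2 on baseline, gender and age. SEs are from the null runs (mean model SE / empirical SE).

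| r | Type I, stated | Type I, adjusted | SE, stated | SE, adjusted | Power, stated | Power, adjusted |
|---|---|---|---|---|---|---|
| 0.3 | 2.6% | 4.3% | 0.431/0.379 | 0.332/0.327 | 44% | 64% |
| 0.5 | 3.3% | 4.2% | 0.365/0.338 | 0.310/0.306 | 57% | 69% |
| 0.7 | 3.8% | 4.8% | 0.282/0.272 | 0.259/0.263 | 80% | 84% |

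The stated model's SE is too large by 14%, 8% and 4% (0.431/0.379, 0.365/0.338, 0.282/0.272). The power gaps are 20, 12 and 4 points. A separate simulation of a change score against ANCOVA at equal SDs gave 45–82% against 61–86%, gaps of 16 to 4 points.

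**5. Unequal SDs, minimisation.** SD 5/6, r = 0.5: power 66% against 70%. SD 4/6, 5-point effect: 57% against 61%, 70% against 70% and 86% against 85% at r = 0.3, 0.5 and 0.7, with type I error of the change score 4.4%, 4.9% and 5.2%.

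**6. If allocation is simple randomisation** (equal SDs, r = 0.5): the stated model's type I error is 5.5% and its SE about right (0.364 against 0.371), but power is still 57% against 67%.

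**The case against.** Four points can be made for the plan.

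- **Baseline is in the model.** A reader might infer that baseline HAM-D-17 is ignored. It is not: T1 is a repeated outcome and the effect is change from baseline. Change-score and baseline-adjusted contrasts are both valid under randomisation; the difference is efficiency. This stands.
- **Selection does little to the primary test.** A reader might infer that the primary result hangs on which demographics happen to differ. With complete data, step 2 shows that it does not. This stands for the interaction. It does not rescue the rule, because the plan expects missing data and uses general linear models for cognition, where such a rule would matter if carried over.
- **The errors are on the cautious side.** A reader might infer error bars that are too narrow and an inflated false-positive rate. The simulations show the reverse where minimisation is used, and near-nominal error where it is not. This stands.
- **The loss may be small.** Entry requires HAM-D-17 of at least 8 (Inclusion Criteria), which cuts off low baseline scores and makes a smaller T1 SD plausible; the gain from adjustment is then slight or nil. This stands as a limit on the size.

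It could also be said that the unnamed confounders may include gender, age or baseline score, and that a covariate list belongs in an analysis plan that is not shown. That excuses the missing list, but not the selection rule, which the article states outright.

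**Conclusion.** The rule is a stated choice that is poorly made. It selects on chance imbalance, is unlikely to admit the factors used to allocate, and leaves baseline HAM-D-17 as an unconstrained T1 outcome.

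The consequence is lost precision, not bias or excess false positives. If minimisation is used, type I error is about 3–4% at equal SDs and 4–5% with a smaller T1 SD. Power at N = 30 is lower than with baseline adjustment by 0 to 16–20 points: most at low correlation with equal SDs, and little or none if the correlation is high or the T1 SD is well below the T2 SD. Most of this comes from how baseline is handled.

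These figures rest on assumed SDs, correlations and effects, since the article gives none. The calibration result also depends on minimisation being the scheme used, which the article leaves unclear. The document does not support a claim of one large, definite loss of power.

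**What to change.** In the Data Analysis Plan, delete the significance-based covariate rule, the open reference to further confounders, and the Wald test of the baseline group difference. Pre-specify gender, age and baseline HAM-D-17 for the primary model in one of two forms:

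- T2 and T3 as outcomes, with baseline HAM-D-17 as a covariate; or
- T1, T2 and T3 as outcomes, with the arms constrained equal at T1.

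Adding gender and age as main effects to the present model would not be enough, because they leave the interaction unchanged. In each secondary model, also include the baseline value of that outcome. Report baseline tables descriptively, without tests.

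Reconcile the Abstract, Trial Design, Concealment Mechanism and Randomisation sections on whether allocation is by minimisation and on which factors. If depression score is not a balancing factor, baseline adjustment is still worth keeping for power.

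The cost is wording and a few degrees of freedom: an ANCOVA with an intercept, arm and three covariates leaves 30 − 5 = 25. Every variable is already collected.

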**Outcomes:**

Baseline measurements and post-TPS evaluation of the psychological outcomes (i.e., depression, cognition, anhedonia, and instrumental activities of daily living) will also be conducted on all participants. A 3-month follow-up period will be used

to assess the long-term sustainability of the TPS intervention. For statistical analysis, ANOVA with repeated measures will be used to analyse data. Missing data were managed by multiple mutations. The level of significance will be set to *p* < 0.05.

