### Objectives

**Primary objective**: To evaluate the effects of TPS on symptoms of depression among young adults in Hong Kong.

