#### Inclusion Criteria

Patients eligible for the trial must comply with all of the following criteria at randomisation: (1) age ≥ 18 years; (2) able to understand/read Chinese; (3) obtain a Hamilton Depression Rating Scale (HAM-D-17) score of ≥ 8.

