#### Primary Outcomes

##### Depression

Hamilton Depression Rating Scale-17 (65) will be used to measure symptoms of depression and participants' mood and depression severity. HAM-D-17 is a widely used reliable measurement of depressive and mood symptoms. Scores will range from 0 to 52, with higher scores indicating more severe depression. Clinical response will be defined as a reduction of 50% or more in the HAM-D-17 score. A HAM-D-17 score of 7 or less will be used as an indicator of remission.

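### The primary outcome, HAM-D-17, has no designated primary time point or joint test, and the abstract names a different analysis model from the methods

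*Protocol article*

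**What the plan says.** The primary objective (Objectives) is "To evaluate the effects of TPS on symptoms of depression among young adults in Hong Kong". It names no visit. Under Primary Outcomes, Depression, the HAM-D-17 "will be used to measure symptoms of depression and participants' mood and depression severity", again with no visit. The same paragraph defines response as a fall of at least half in the score, and adds "A HAM-D-17 score of 7 or less will be used as an indicator of remission".

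The Data Analysis Plan sets a two-level model for Objective 1 (time points within respondents) to "investigate changes in the outcome measures (depression) at each time interval (2 weeks and 3 months) with respect to their baseline measurements". The fixed part is to "estimate change from baseline to 2 weeks and from baseline to 3 months", and interaction terms, in the plural, carry the TPS effect over time. For every test, p-"values of < 0.05 (two-tailed) will be considered significant". A generalised Wald test is mentioned, but for Objectives 2, 3 and 4 only. The section gives no analysis of response or remission. It names repeated-measures ANOVA once, for the Trail Making Test.

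The abstract (Outcomes) says instead that "ANOVA with repeated measures will be used to analyse data".

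**The concern.** With two post-baseline visits there are two arm-by-time contrasts on the primary outcome. Each has its own 5% chance of a false positive, and nothing says which one counts. A reader of the results could not tell whether a positive finding at one visit, with nothing at the other, meets the primary objective. The choice could be made after the results are known.

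The stakes are higher than the pilot label suggests. The abstract says the results will inform policy on whether TPS could be a top treatment option for MDD, and Sample Size Estimation says the 30 subjects are recruited to evaluate efficacy.

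Two smaller points belong with this. The abstract and the methods name different models for the main analysis, so the article does not state one primary analysis consistently. Response and remission appear under the primary heading, so their status is unclear.

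**Working it through.** **Inputs from the protocol article.** Two-sided alpha of 0.05 for each test; two contrasts on HAM-D-17 (baseline to 2 weeks, baseline to 3 months); 30 participants allocated 1:1, so 15 per arm. No power, effect size or SD is given, so there is no sample-size figure to reproduce. The one stated figure is the 0.05, and it holds as an overall error rate only for a single test: 1 − (1 − 0.05)^1 = 0.05.

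**Correlation between the two contrasts.** The described model has one respondent-level variance. Read as a random intercept with constant residual variance s² and complete data, the scores are Y1 = b + e1, Y2 = b + e2 and Y3 = b + e3. The changes are e2 − e1 and e3 − e1. Each has variance 2s² and their covariance is s², so the correlation is s² / 2s² = 0.5. The arm differences in these changes have the same correlation.

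**False-positive rate if either visit counts.** This is P(|Z1| > 1.96 or |Z2| > 1.96) for a standard bivariate normal pair with correlation r. For r = 0 it is 1 − 0.95² = 0.0975. For other values:

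| r | rate |
|---|---|
| 0.3 | 0.095 |
| 0.5 | 0.091 |
| 0.7 | 0.083 |
| 0.8 | 0.078 |
| 0.9 | 0.070 |

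Only r = 0.5 follows from the described model. The other values are assumptions that show the range.

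**What each remedy costs with 15 per arm.** By the normal approximation, the effect detectable at 80% power in SD units is (z for alpha + 0.842) × √(2/15), where √(2/15) = 0.365.

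- One test at 0.05: (1.960 + 0.842) × 0.365 = 1.02 SD.
- Both visits kept, Bonferroni 0.025 each: (2.241 + 0.842) × 0.365 = 1.13 SD.

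For an assumed true effect of 0.8 SD, power is 59% with one test at 0.05 and 48% at 0.025. Naming one test therefore controls the error without this loss.

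**The two model statements side by side.** The abstract applies repeated-measures ANOVA to the data in general. The Data Analysis Plan applies a two-level model to depression, extends the same model to the secondary outcomes, and keeps repeated-measures ANOVA for one cognitive test. Both cannot describe the primary analysis.

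**The case against.** The strongest reply is that the plan fits one model, in which a single joint group-by-time test is available, and that choosing it or ranking the visits is often left to a statistical analysis plan, which is not shown here. The 0.05 is a per-test threshold, and the article claims no family-wise control. This has some force: a separate plan may already settle the matter. But the article does not defer the question. It sets out the model, the two changes from baseline, the number of imputations and the threshold for all tests, and on those terms either visit can be read as decisive. The abstract conflict lies within this document whatever another plan says.

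Four stronger readings are tempting and should not be made.

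- *Response and remission are each tested at 0.05.* The article only defines them. No test is planned, so they cannot be counted in the error rate. What can be said is that their rank and analysis are undefined.
- *Remission is too easily reached by measurement noise.* Entry requires participants to "obtain a Hamilton Depression Rating Scale (HAM-D-17) score of ≥ 8", one point above the remission cut-off. But nobody enters in remission, noise would affect both randomised arms alike, and any figure would need a measurement SD and true score that the article does not give.
- *The two models conflict because they treat incomplete participants differently.* The abstract, the Data Analysis Plan and the missing-data section all intend multiple imputation (the abstract's wording appears to be a slip). On completed data the two can coincide: in three simulated complete datasets (15 per arm, three visits, no covariates), the ANOVA group-by-time F and the random-intercept joint Wald statistic divided by 2 agreed to four significant figures. They may still differ through covariates, sphericity handling or single-visit contrasts.
- *T3 is certainly not a treated-versus-untreated comparison.* All participants receive TPS, and the waitlist arm may have been treated by T3. The exact timing is in the flow diagram (Figure 5), which is not shown, so this remains a possibility.

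**Conclusion.** The point holds for the two visits and for the abstract. With no primary visit, joint test, ranking or adjustment for Objective 1, a claim resting on either visit carries a false-positive risk of about 9% instead of 5%. The 9.1% rests on a random-intercept reading of the model with complete data; assumed correlations of 0.8 to 0.3 give 7.8% to 9.5%. The figure applies only if success at either visit is allowed to count, which the article neither states nor rules out. The abstract's model does not match the methods and should be corrected. The unclear standing of response and remission is a gap in labelling and adds nothing to the computed error rate. This should be changed, though it does not invalidate the design.

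**What to change.** Before any arm comparison is seen, and with the change dated (Trial Status says recruitment is complete, and Interim Analyses gives the principal investigator access to all data):

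1. In the Data Analysis Plan, name one primary test: the arm difference in HAM-D-17 change from baseline to T2, from the two-level model, at two-sided 0.05. A single joint group-by-time test on 2 degrees of freedom would also hold 5%. T2 is preferable because everyone eventually receives TPS (Explanation for the Choice of Comparators; Intervention Description; Limitations) and the waitlist arm may already be treated by T3.
2. Label T3, response and remission as supportive, reported with confidence intervals and without a success claim.
3. Change the abstract to name the two-level model for the main analysis.

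The cost is wording, and alpha is not split across the 30 participants. The downside is that a significant T3 result alone could no longer be presented as a positive primary result.

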**Secondary objectives**:

To improve young adults' anhedonia symptoms after the 2-week TPS intervention and will be maintained at 3-month post-intervention follow-upTo improve young adults' instrumental activities of daily living (IADL) after the 2-week TPS intervention and will be maintained at 3-month post-intervention follow-up.To improve young adults' cognition after the 2-week TPS intervention and will be maintained at 3-month post-intervention follow-up.Post-MRI scan will show a remarkable structural and functional connectivity in participants' brains after the 2-week TPS intervention compared to pre-MRI scan.

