#### Cognition

Global cognition will be measured using the Hong Kong Chinese version of the Montreal Cognitive Assessment (MoCA) (68). The MoCA is a one-page test with a maximum score of 30. One point is added if the person has 12 years of education or less. A score of 23–26 represents mild cognitive impairment, 17–22 represents moderate impairment, and 16 or below suggests severe impairment and dementia. Working memory, executive function, and attention will be measured by forward and backward digit span, the category verbal fluency test, and the Trail Making Test (TMT) Parts A and B.

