### Sample Size

#### Sample Size Estimation

To the best of our knowledge, there is only one TPS uncontrolled pilot study conducted on 35 patients with AD in Austria (60). Therefore, we cannot base on their effect size to estimate our sample size in this study. Considering the nature of our study is the first pilot RCT in using TPS in the treatment of depression, and also referenced by Beisteiner's study, we aim to recruiting 30 subjects to evaluate the efficacy of our primary and secondary outcomes in this study.

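### The plan calls every secondary test significant at p < 0.05, across at least eight measures at two visits, with no lead measure or exploratory label and with overlapping analyses of the cognitive tests

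*Protocol article*

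**What the plan says.** All references are to the protocol article.

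- **Threshold.** The Data Analysis Plan states: "In all tests, significant differences between groups will be detected with a 95% CI", and p-values "of < 0.05 (two-tailed) will be considered significant". The Abstract repeats the 0.05 level.
- **Models.** For the secondary measures: "The same model, which will be conducted separately for each outcome, will be used to investigate the effect of interventions on secondary outcome measures". The model estimates change from baseline to 2 weeks and to 3 months, with interaction terms for the effect of TPS over time. For Objectives 2, 3 and 4, "pairwise comparison and other hypotheses on the intervention effects will be tested using a generalised Wald test".
- **Measures.** The outcome sections give SHAPS for anhedonia, the Lawton scale for IADL and MoCA for global cognition. They add: "Working memory, executive function, and attention will be measured by forward and backward digit span, the category verbal fluency test, and the Trail Making Test" Parts A and B.
- **Further cognitive analyses.** The Data Analysis Plan also compares digit span, a Stroop test, verbal fluency and TMT between groups by a general linear model (GLM). It then assigns TMT to a repeated-measures ANOVA. The Stroop test does not appear under Cognition.
- **Status of the secondary outcomes.** They are worded as efficacy aims, for example "To improve young adults' cognition after the 2-week TPS intervention and will be maintained at 3-month post-intervention follow-up". Sample Size Estimation says "we aim to recruiting 30 subjects to evaluate the efficacy of our primary and secondary outcomes in this study".
- **Error control.** The only family-wise correction is in the Neuroimaging section, for voxel-wise comparisons.

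**The concern.** This is not a gap that a later analysis plan would simply fill. The protocol sets a rule: full alpha for every test. A hierarchy added later would have to override that sentence.

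Because the secondary objectives are phrased as improvements to be shown, one nominal p-value among many could be reported as an effect of TPS on anhedonia, daily function or cognition, even if HAM-D-17 shows nothing. Objective 4 is the most exposed. It has six collected measures (seven with Stroop), none is named as deciding it, and the individual tests have two or three possible analyses from which a result could be chosen.

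**Working it through.** The protocol states no family-wise error rate, so there is no planned figure to reproduce.

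**Inputs from the protocol**
- Level per test: 0.05 two-sided, so 0.025 in the tail favouring TPS.
- Measures for Objectives 2 to 4: SHAPS (1) + IADL (1) + MoCA (1) + digit span forward and backward (2) + verbal fluency (1) + TMT-A and TMT-B (2) = 8. With Stroop, 9.
- Post-baseline visits: 2.

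**Assumption, not in the protocol.** The test statistics are equicorrelated normal with correlation r. Results are shown for r = 0 to 0.8.

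**Number of tests.** The Wald wording does not fix it. One test per measure per visit gives 8 × 2 = 16. One test per measure gives 8.

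**Formulas.** For k independent tests, the chance of at least one false result in either direction is 1 − 0.95^k, and in favour of TPS it is 1 − 0.975^k.
- k = 16: 1 − 0.95^16 = 56.0%; 1 − 0.975^16 = 33.3%.
- k = 8: 1 − 0.95^8 = 33.7%; 1 − 0.975^8 = 18.3%.

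For r > 0 the same probabilities were obtained by integrating over the shared normal component.

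| Tests | Event | r = 0 | r = 0.3 | r = 0.5 | r = 0.8 |
|---|---|---|---|---|---|
| 16 | either direction | 56% | 48% | 37% | 21% |
| 16 | in favour of TPS | 33% | 24% | 19% | 10% |
| 8 | either direction | 34% | 30% | 25% | 16% |
| 8 | in favour of TPS | 18% | 15% | 12.5% | 8% |

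A joint two-visit Wald test has no direction of its own. The last row therefore treats each measure as giving a single signed statistic.

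**Against the nominal rates.** At r = 0.5, 16 contrasts give 37/5 = about 7 times the nominal rate in either direction, and 19/2.5 = about 7.5 times in favour of TPS. In the mildest cell (8 tests, r = 0.8) the ratios are 16/5 and 8/2.5, each about 3.

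**Left out of the counts.** The Stroop test, the GLM and ANOVA re-analyses, other pairwise comparisons, and the subgroup analyses of primary and secondary outcomes mentioned under Methods for Additional Analyses. Each would raise the figures.

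**Overlapping analyses, side by side**

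| Measure | Multilevel model (as a secondary outcome) | GLM | Repeated-measures ANOVA |
|---|---|---|---|
| Digit span forward and backward, fluency | yes | yes | no |
| TMT-A, TMT-B | yes | yes | yes |
| Stroop | not a listed outcome | yes | no |

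**The case against.** **A stronger reading: 37% of null trials would wrongly show that TPS improves a secondary outcome.** The figure does not support this. It counts false differences in either direction. For 16 tests the favourable-direction chance is 33% even under independence, and positive correlation lowers it to about 19% at r = 0.5.

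**A second stronger reading: the protocol lets any one of 16 p-values meet a secondary objective.** It does not say so. Each objective asks for improvement after treatment that is also maintained at 3 months. Read literally, that requires both visits. Under that rule, a favourable result at both visits on at least one of eight measures has a chance of about 3% to 8%, assuming correlation 0 to 0.5 between measures and 0.5 to 0.8 between visits. This stands as a real limit: the size depends on a success rule that the protocol never states. But the significance sentence applies to each test and does not require both visits.

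**It is a pilot with one primary scale, and unadjusted secondary outcomes are common.** It is true that HAM-D-17 is the single primary measure, and this limits the severity. The pilot label does not settle the matter, because the sample size section gives efficacy on the secondary outcomes as the aim.

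**A multiplicity rule can be left to an analysis plan.** Its absence alone would be no finding. Here the protocol states the opposite rule and itself prescribes the overlapping cognitive analyses.

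**Gating behind HAM-D-17 at 2 weeks would be a matter of preference.** Agreed. It would also drop the maintenance half of each objective, so it is not proposed.

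**Conclusion.** The concern holds in limited form. The protocol gives full two-tailed 0.05 to every test on at least eight secondary measures at two visits, names no lead measure, labels nothing exploratory, and analyses the individual cognitive tests in two or three ways. On the 16-contrast reading and an assumed equicorrelation of 0.5, at least one false significant difference arises in about 37% of trials with no effect, and one in favour of TPS in about 19%. On the one-test reading the figures are 25% and 12.5%.

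The correlation and the number of tests per measure are assumptions, so the ranges matter more than any single value. The point bears on what may be concluded about anhedonia, function and cognition. It should be corrected, but it does not threaten the primary analysis.

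**What to change.** 1. Limit the sentence that applies to all tests, so that p < 0.05 denotes significance for the primary outcome only.
2. State that Objectives 2 to 4 are exploratory, reported at both visits as between-group estimates with 95% CIs and without efficacy claims. If a secondary claim is wanted, name one measure and one test for each objective and apply Holm across the three at an overall two-sided 0.05 (first step 0.05/3 = 0.0167).
3. Name the one cognitive measure that decides Objective 4.
4. Use one analysis per cognitive test, the multilevel model, and drop the duplicate GLM and ANOVA. Either list the Stroop test as an outcome or remove it from the analysis.

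These are wording changes that need no new data. Trial Status reports recruitment as complete, so they should be made and dated before outcomes are compared by group. The cost is that isolated nominal secondary p-values can no longer be reported as efficacy findings and, under the Holm option, a secondary result faces a stricter first threshold.
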